**Study Instruments and Variables**

Respondents from all study branches will have the opportunity to complete baseline, post-intervention and follow-up assessments, which based upon previous piloting activities, each average about 10 minutes in duration. Survey questions have been adapted from questionnaires used by the research team in their previous online studies and pilot intervention. The online baseline and follow-up questionnaires will include information on the following domains:

- demographics (year of birth, race/ethnicity, education, income and the first 3 digits of the US zip code)

- depression and anxiety symptomatology

- assessment of risk behaviors, such as type of sexual contact (anal, oral, vaginal -- with and without condoms)

- knowledge of partners’ HIV status and disclosure of participants’ HIV status

- drug and alcohol use (in general and use before or during sex)

- how sex partners were met (online versus other ways)

- HIV and STD testing

- knowledge of HIV status

Please see ‘Additional Outcome Variables’ under Primary and Secondary Outcome Variables below. All surveys are located in the Appendices.

**Standardized Measures Included in Instruments**

Depression and Anxiety Symptoms: The Patient Health Questionnaire for Depression and Anxiety (PHQ-4)51 is a four-item scale that will be used. The PHQ-4 comprises the PHQ-2, which assesses depressed mood and anhedonia, and the GAD-2, which assesses generalized anxiety disorder. The PHQ-4 begins with the stem question: “Over the last 2 weeks, how often have you been bothered by the following problems?” The four screening questions are: Feeling nervous, anxious, or on edge; Not being able to stop or control worrying; Feeling down, depressed, or hopeless; and Little interest or pleasure in doing things. Responses are scored as 0 (“not at all’), 1 (“several days”), 2 (“more than half the days”), or 3 (“nearly every day”). The total score on this composite measure ranges from 0 to 12 (the score range for both the PHQ-2 and GAD-2 is 0 to 6). Kroenke and colleagues measure depression and anxiety screens separately. Thus, if a participant scores 3 or higher on either the PHQ-2 or the GAD-2, then he will have screened positive for that mental health problem. A score of 3 is considered the optimal cut-point for screening purposes.52, 53

Reasons for Not Getting Tested: We will be using a slightly adapted version of the CDC sponsored HIV testing Survey (HITS), which inquires about the various reasons people don’t get tested. The instrument targets HIV-negative or untested individuals at-risk for HIV infection.

Defining Sex Partners:The definition of male or female main partner for this study is: Main Partner (boyfriend [or girlfriend], spouse, significant other, or life partner). This definition will be used for the 60 days prior to and after baseline. We will be able to determine new partners (first sex within the past 60 days) from the question, “When did you first have sex with xxx?” The response options are (‘within the last’) 24 hours, 7 days, 30 days, 60 days, 1 year, more than a year ago. If the respondent chooses 60 days or sooner, then we know this was a new partner.

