**Informed Consent Procedures**

The informed consent process for this study is in 2 parts: 1) Participants who click on a banner ad will be required to review and complete the online informed consent by clicking a button that indicates they read the consent form and wish to participate in the baseline survey. The consent form will state that the study is limited to persons aged 18 or older, for men who have sex with men, and addresses substance use and sexual risk behaviors associated with HIV transmission. Men who provide informed consent by clicking the consent form button will be allowed to enter the online baseline survey.

2) If the participant meets criteria for the intervention study (which will be automatically programmed to identify eligible participants), he will see another consent form that will invite him to participate in a brief intervention and ask for his email address. He will be informed that the study is randomized, and a brief description will be given for the study branches. If the participant consents by clicking the consent form button, then he will automatically be randomized into one of the assigned conditions. Before the participant begins the intervention, he will see information that clearly describes the assigned condition (i.e., prevention web page or video). For those who are assigned to the control condition, a screen will appear with the post-intervention questions, and then they will see a statement about being contacted in 60 days for a follow-up survey.

Intervention participants will be contacted via email 60 days post-intervention to complete the follow-up survey. A hyperlink will be embedded in the email, and when clicked on, will automatically transfer the participant to the consent reminder, which highlights the same information from the second consent. Men are given the opportunity to go on to the next page to begin the survey or to close their browser. Participants will be able to print copies of the consent forms and the reminder.

For participants who do not respond to the follow-up email, we will wait approximately 1 week before sending a first reminder email, approximately another week before sending the second reminder, and approximately one more week before sending the final reminder email (for an additional total of 21-30 days). The maximum number of days for completion of the follow-up survey will be 75 days.

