**Primary and Secondary Outcome Variables: Baseline & (60-day) Follow-up Period**

These questions will be included in the baseline survey and the 60-day follow-up surveys

| **Concept** | **Number of Key Variables** | **Primary Outcome Variables** | **Measurement for Statistical Analysis** |
| --- | --- | --- | --- |
| HIV Disclosure: Asked partner(s); partners asked | 4 variables | Likert scale for “asking HIV status” by partner serostatus | (Ordinal), Treated as Continuous |
| HIV Disclosure: Told partner(s); partners told | 4 variables | Likert scale for “telling HIV status” by partner serostatus | (Ordinal), Treated as Continuous |
| HIV testing / Reasons for not getting tested | 10 variables | Number of times tested, last time tested and test result, if HIV negative or unknown will respondent plan to get tested and when? If never tested, reasons for not testing. If HIV-positive, when did they get test result (month/year). | Categorical |
| Current Condom Use | 8 variables | Condom use (receptive and insertive) with new and/or steady partners in past 60 days. | Categorical |

| **Concept** | **Number of Key Variables** | **Secondary Outcome Variables** | **Measurement for Statistical Analysis** |
| --- | --- | --- | --- |
| Drug Use | 15 drugs | Frequency of drug use and typical drugs (route of administration) used in past 60 days. | Continuous, categorical |
| Alcohol Use | 4 variables | Frequency of alcohol use and number of drinks drank (binge drinking) (5+ drinks) before/during sex and in general past 60 days. | Continuous, categorical |
| Depressive Symptoms, last 2 weeks | 2 variables | Positive Depressive Symptom Score: PHQ-2, part of PHQ-4. | Interval (Will be dichotomized) |
| Anxiety Symptoms, last 2 weeks | 2 variables | Positive Generalized Anxiety Disorder Score: GAD-2, part of PHQ-4. | Interval (Will be dichotomized) |
| **Concept** | **Number of Key Variables** | **Additional Variables** | **Measurement for Statistical Analysis** |
| Drug or alcohol treatment | 1 variable | 60-day drug or alcohol treatment (yes, no) | Dichotomous |
| Health seeking behavior | 2 variables | Clicks on treatment links on the survey exit page- do the proportion of clicks vary by intervention branch? | Dichotomous |

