**DATA HANDLING AND ANALYSIS**

Although no personally identifying information other than email addresses (which will be encrypted and stored separately), will be collected at any point during the surveys, several technical steps will be taken to ensure the security and privacy of data in general. All survey data will be stored on a secure Public Health Solutions web server with firewalls and industry standard protections and will be removed from the web server at the end of the survey period.

All analyses will be performed in SPSS 14.0 and SAS 9.1 for Windows. For the overall sample (3,000) we will use a reduced alpha level (.01) as a criterion for statistical significance. For the within-branch analyses (n=600 or less) we will use the conventional alpha level (.05). Due to decreased power, all interaction tests will be conducted at the 0.10 level of significance.

The first analytic procedure will be to use ANOVA or chi-square to compare key characteristics (i.e., age, race/ethnicity, income) among and between the 5 randomized groups to ensure that there are no statistical differences, and to verify that computerized randomization worked.

**Frequency Distributions**: Frequency distributions will be produced for all variables and be used to describe the sample characteristics and answer key questions (e.g., what percentage of men reported unprotected anal or vaginal intercourse in their last sexual encounter with a new male or female partner?).

**Bivariate Analysis:** Bivariate analysis will be conducted to identify measures that show significant associations with primary outcome variables, (e.g., asking or telling HIV status to new sex partners [yes/no], HIV testing during the 60 days after baseline [y/n], and unprotected anal or vaginal intercourse [y/n]). Associations between measures with more than two values (e.g., drug use increased, decreased, or remained the same) and binary outcomes (e.g., HIV/STI testing [y/n]) will be tested, though the Pearson Chi-Square test and t-tests will be performed with continuous variables (e.g., number of sex partners in past 60 days).

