**The following items are included in the baseline survey but excluded from the follow-up:**

I am a... (Gender)

How would you describe your sexual orientation?

Where do you live?

The city that I live in has...

My annual income is:

Are you currently employed?

How many times have you moved in the past year?

Have you ever had oral or anal sex with a male?

Have you ever had oral, vaginal, or anal sex with a female?

Past year / Lifetime Sexual history questions for males and females

About how old were you when you first had a drink?

In your lifetime: have you ever injected...

In your lifetime: have you ever had a blood transfusion?

In your lifetime: have you ever been tested for Hepatitis B?

In your lifetime: have you ever been vaccinated for Hepatitis B?

In your lifetime: have you ever been tested for Hepatitis C?

How many times have you been tested for HIV?

Do you have a primary care provider?

Do you currently have health insurance?

Have you ever spent at least 1 night in jail or prison?

Which best describes your weight?

**The following items are included in the baseline survey but the time period will be modified to the past 60 days for the follow-up survey:**

In the past 60 days...

Have you been diagnosed with the following?

Have you had mental health counseling or treatment from a mental health provider? y/n

Have you attended any alcohol or drug treatment programs (such as twelve-step program)? y/n

(please specify)________

Have you seen an online video about HIV? (check all that apply)

□ Yes, in this study

□ Yes, on Youtube

□ Yes, on another website (please name the site)__________

Following completion of the baseline survey participants will be provided with the following instructions depending upon eligibility to continue further:

If ineligible, the participant will receive a message saying, “Thank you for your time. We appreciate your input in this study. Here are some links to helpful websites about staying healthy. Please check back on the MHRA website in 2008 for a description of the study’s results.”

If eligible, the participant will automatically be directed to the C-2 Consent Form.

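### Men who answer the follow-up after day 60 are asked about a window that omits their first post-intervention days, and partners first met in those days are coded as not new

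*Protocol*

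**What the plan says.** Two kinds of reference period appear in the Protocol.

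*Counted back from the day of answering.* Standardized Measures Included in Instruments says "We will be able to determine new partners (first sex within the past 60 days) from the question" on when the man first had sex with that partner. The options are "24 hours, 7 days, 30 days, 60 days, 1 year, more than a year ago", and the coding rule is "If the respondent chooses 60 days or sooner, then we know this was a new partner". The outcome table lists "Condom use (receptive and insertive) with new and/or steady partners in past 60 days", and the drug, alcohol and new-partner-count entries use the same 60-day look-back. Appendix E adds a group of items for which "the time period will be modified to the past 60 days for the follow-up survey". One of them asks whether the man has seen an online HIV video, and one of its answer options is a video seen in this study.

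*Counted forward from baseline.* Under Bivariate Analysis in Data Handling and Analysis, the testing outcome is given as "HIV testing during the 60 days after baseline [y/n". Of the main-partner definition, the Protocol says "This definition will be used for the 60 days prior to and after baseline". The intention questions in Appendix F also look 60 days ahead.

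*When men answer.* Under Informed Consent Procedures the email is sent 60 days after the intervention. Weekly reminders follow over a further 21–30 days, and then: "The maximum number of days for completion of the follow-up survey will be 75 days".

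**The concern.** The two reference periods coincide only for a man who answers on day 60. Nobody is invited earlier, and the reminders exist to collect answers later. For every later answer the look-back slides forward and leaves a gap just after the intervention.

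Three things are at stake:

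- **Lost behaviour.** The intervention is a single short exposure. Any effect that shows early is partly outside the window for late responders.
- **Partner classification.** The first primary hypothesis concerns disclosure with *new* partners, and condom use is recorded for new and/or steady partners. A partner first met soon after the intervention can be coded as not new only because the man answered late.
- **The exposure item.** The study video was shown on day 0. A man in branches 3–5 who answers after day 60 cannot truthfully say that he saw it in the past 60 days.

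**Working it through.** **Inputs.** Day 0 is the day of the intervention. Baseline, second consent and intervention follow one another directly, so it serves as the baseline day too. Invitation on day 60, first reminders about a week apart, a further 21–30 days of reminders and a 75-day maximum all come from Informed Consent Procedures. The look-back is 60 days. I take the 75 days as counted from the intervention; the text does not name the starting point.

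**Step 1: can the 75-day maximum be reproduced?** No. Three weekly reminders reach 60 + 7 + 7 + 7 = day 81, and the stated 21–30 days reach day 81 to 90. The two statements stand in the same section and disagree. I use 75 below.

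**Step 2: days not covered.** A man answering on day t is asked about days t − 60 to t, so the first t − 60 days are not covered.

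| Answer day t | Days missed, t − 60 | Share of first 60 days, (t − 60)/60 | Share of time since intervention, (t − 60)/t |
|---|---|---|---|
| 60 | 0 | 0% | 0% |
| 67 | 7 | 7/60 = 12% | 7/67 = 10% |
| 74 | 14 | 14/60 = 23% | 14/74 = 19% |
| 75 | 15 | 15/60 = 25% | 15/75 = 20% |

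**Step 3: partner coding.** A man answering on day 75 who first had sex with a partner on day 5 did so 75 − 5 = 70 days ago. He must choose 1 year, and the partner is coded not new. No option lies between 60 days and 1 year, so that answer cannot be told apart from a partner who predates the study. With acquisition even over time (assumption), the last column of the table is the share of post-intervention new partners miscoded: 20% at day 75.

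**Step 4: men rather than partners.** Assume a constant Poisson rate of m new partners per 60 days. Among men with at least one new partner since the intervention, the share coded as having none is 1 − (1 − e^(−m)) / (1 − e^(−mt/60)).

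- t = 75, m = 0.5: 1 − 0.393/0.465 = 15%
- t = 75, m = 1: 1 − 0.632/0.713 = 11%
- t = 75, m = 4: 1 − 0.982/0.993 = 1%
- t = 67: from 8% (m = 0.5) to under 1% (m = 4)

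**Step 5: if behaviour change comes early.** Suppose event times are exponential with mean μ days (assumption). The share of events in the first 60 days that is missed is (1 − e^(−(t−60)/μ)) / (1 − e^(−60/μ)). At day 75 this is 46% for μ = 30 and 56% for μ = 20, against 25% with even timing. At day 67 it is 24% and 31%, against 12%.

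**Step 6: which outcomes are touched.**

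- *New-partner count, condom, drug and alcohol items:* directly, by the stated look-back.
- *Disclosure:* no look-back is stated. It is reached only through which partners count as new.
- *HIV testing:* collected as the time of the last test and scored from baseline, so loss is not shown. However, Appendix E drops the number-of-tests item at follow-up, and the outcome table classes testing as categorical. Whether the outcome can be scored exactly depends on an answer format that is not shown.
- *PHQ-4:* a two-week window, unaffected.

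**The case against.** The strongest reply is that equal 60-day look-backs at two time points are a conventional and coherent design. The outcome table puts the same questions in both surveys, and the hypotheses concern change between them. The anchor on baseline is stated only for testing and for the main-partner definition. This stands, and it limits the remedy. An open window since the intervention would make follow-up recall 60–75 days against 60 at baseline. Any-event and count outcomes would then rise from longer exposure alone, and the within-branch McNemar comparisons would be distorted. The reply does not answer the partner coding, the different anchor for testing, or the video item.

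A second reply is that the rule is identical in every branch. That also stands. With equal response timing and no true effect, it creates no difference between branches. A reader might infer bias along the primary contrast because Attrition and Retention Efforts expects 40% attrition in branches 1–2 and 30% in branches 3–5. That section predicts who will be lost, not when the others answer, so the inference is not supported.

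A reader might also infer losses of 35–50% of the window from answers on days 81–90 (21/60 and 30/60). Those answers fall beyond the stated maximum, and whether they would be accepted is part of the Step 1 conflict.

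Finally, the survey is a separate file that is not shown, so exact item wording cannot be checked. The video item and the other re-worded Appendix E items are not primary or secondary outcomes.

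**Conclusion.** The point holds for the look-back items and the new-partner rule. For a man answering after day 60, the first t − 60 days are not observed, up to 15 days or 25% of the first 60 at the 75-day maximum. With even acquisition, up to 20% of his post-intervention new partners are coded not new. The average over the trial depends on when men answer, which the Protocol does not give.

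The consequence is possible dilution of early effects and misclassified new partners. It should not be read as a demonstrated loss in all three primary outcomes, nor as a demonstrated difference between branches. The look-back never reaches before the intervention, so there is no contamination from baseline behaviour. The conclusion rests on the Protocol's own description of the items and on counting the 75 days from the intervention. It matters before launch because the first-sex categories, once collected, cannot be refined.

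**What to change.** Keep a 60-day reference period of the same length as at baseline, and change four things:

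1. In the follow-up first-sex item, keep the existing options and add a category cut at the man's stored intervention date. A partner first met more than 60 days ago but after that date can then be identified as new. Baseline comparisons of counts can still use the 60-day categories.
2. Record the date of the last HIV test, so that testing in the 60 days after baseline can be scored. If that date falls after day 60, one further yes/no question on an earlier test since the intervention is needed.
3. Re-word the video item to *since you joined this study on [date]*.
4. Use days from intervention to response only in a sensitivity analysis. It is measured after randomisation and should not be a covariate in the primary model.

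Do not convert every item to an open window since the intervention date. If behaviour items are to be anchored, use *the 60 days after [date]*, which keeps the length equal to baseline.

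The cost is slightly more complex items, piping one stored date into the survey, and an IRB amendment. Separately, the 75-day maximum and the 21–30 day reminder period must be reconciled, since they set the largest possible gap (15 or up to 30 days). Reconciling them caps the gap but does not remove it.

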**Primary and Secondary Outcome Variables: Baseline & (60-day) Follow-up Period**

These questions will be included in the baseline survey and the 60-day follow-up surveys

| **Concept** | **Number of Key Variables** | **Primary Outcome Variables** | **Measurement for Statistical Analysis** |
| --- | --- | --- | --- |
| HIV Disclosure: Asked partner(s); partners asked | 4 variables | Likert scale for “asking HIV status” by partner serostatus | (Ordinal), Treated as Continuous |
| HIV Disclosure: Told partner(s); partners told | 4 variables | Likert scale for “telling HIV status” by partner serostatus | (Ordinal), Treated as Continuous |
| HIV testing / Reasons for not getting tested | 10 variables | Number of times tested, last time tested and test result, if HIV negative or unknown will respondent plan to get tested and when? If never tested, reasons for not testing. If HIV-positive, when did they get test result (month/year). | Categorical |
| Current Condom Use | 8 variables | Condom use (receptive and insertive) with new and/or steady partners in past 60 days. | Categorical |

| **Concept** | **Number of Key Variables** | **Secondary Outcome Variables** | **Measurement for Statistical Analysis** |
| --- | --- | --- | --- |
| Drug Use | 15 drugs | Frequency of drug use and typical drugs (route of administration) used in past 60 days. | Continuous, categorical |
| Alcohol Use | 4 variables | Frequency of alcohol use and number of drinks drank (binge drinking) (5+ drinks) before/during sex and in general past 60 days. | Continuous, categorical |
| Depressive Symptoms, last 2 weeks | 2 variables | Positive Depressive Symptom Score: PHQ-2, part of PHQ-4. | Interval (Will be dichotomized) |
| Anxiety Symptoms, last 2 weeks | 2 variables | Positive Generalized Anxiety Disorder Score: GAD-2, part of PHQ-4. | Interval (Will be dichotomized) |
| **Concept** | **Number of Key Variables** | **Additional Variables** | **Measurement for Statistical Analysis** |
| Drug or alcohol treatment | 1 variable | 60-day drug or alcohol treatment (yes, no) | Dichotomous |
| Health seeking behavior | 2 variables | Clicks on treatment links on the survey exit page- do the proportion of clicks vary by intervention branch? | Dichotomous |
| Intention to Change Behaviors: Post-Intervention Assessment | 4 variables | Within the next 60 days…How likely are you to: use condoms with new sex partners? ASK your new sex partners their HIV status? TELL your new sex partners your HIV status? (if negative or untested) Get an HIV test? | Continuous |
| New Partners | 2 variables | Number of NEW male or female sex partners in past 60 days prior to baseline and 60-day follow-up. | Continuous |
| Diagnosis of Depression, Anxiety, and other conditions | 10 variables | Ever diagnosed – qualitative option for diagnoses not listed | Dichotomous |
| Past 60-day mental health counseling | 1 variable | If yes, past 60 days, or longer than 60 days ago. | Categorical |
| Current medications |  | Checkbox selection of medications plus “other medication” qualitative option for medications not on list | Categorical, string |

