**Intended/Potential Use of the Study Findings**

A recent study comparing the cost-effectiveness of HIV prevention interventions found that the two most important factors that determined cost-effectiveness were the HIV prevalence of the target population and the cost per person reached.30 In fact, one of the two most cost-effective interventions overall was showing videos in STI clinics (individual-level).30 These findings support our proposed online behavioral intervention using video vignettes in terms of cost-effectiveness and reaching high-risk MSM. If successful, this type of novel Internet-based intervention approach will be efficient, cost-effective, feasible to replicate, and especially useful in reaching men in rural areas or other hard-to-reach populations.

Specific Aims and Hypotheses

**Aim 1:** To test the feasibility of implementing an innovative national online randomized controlled, multi-branched, behavioral intervention for men who have reportedoral or anal sex with any male (new partner or not) in the past 60 days AND reported oral, anal or vaginal sex for the first time (new partner) with a male or female within the past 60 days.

**Aim 2:** a) To identify and recruit men who have sex with men met online or offline, and who, in the last 60 days, met a new sex partner; b) To enroll and randomly assign 3,000 MSM, representing diverse race/ethnicities and geography, into one control or four intervention conditions; c) To maximize retention 60-days post-intervention to complete the follow-up survey.

**Aim 3:** To evaluate the intervention conditions by comparing outcome risk measures (HIV disclosure, HIV testing, condom use, drug and/or alcohol use before sex, and depressive and/or anxiety symptomatology) at 2 time points for 5 study conditions.

**Aim 3 Primary Hypotheses:** Between baseline and 60-day follow-up there will be an increase in the following: a) HIV disclosure with new sex partners, b) HIV testing, and c) condom use in intervention branches 3, 4, and 5, compared to branches 1 and 2.

**Aim 3 Secondary Hypotheses:** Between baseline and follow-up, there will be a decrease in the following: a) drug use before sex, b) alcohol use before sex, and c) depressive and/or anxiety symptomatology in intervention branches 3, 4, and 5, compared to branches 1 and 2.

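### The primary asking and telling scores are split by partner serostatus, which asking and telling can themselves change; the split also conflicts with the unsplit disclosure outcome used for power and modelling

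*Protocol*

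**What the plan says.** In the Protocol section on primary and secondary outcome variables, the two disclosure rows give the primary outcome variables as "Likert scale for “asking HIV status” by partner serostatus" and "Likert scale for “telling HIV status” by partner serostatus". Each row has four variables, collected at baseline and at 60 days, and the measurement column reads "Ordinal), Treated as Continuous".

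The section on study instruments and variables lists "knowledge of partners’ HIV status and disclosure of participants’ HIV status" among the survey domains. It mentions no other source for a partner's status.

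Other sections describe the disclosure outcome without a split:

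- **Specific Aims and Hypotheses**, Aim 3 primary hypotheses: "a) HIV disclosure with new sex partners".
- **Sampling, Sample Size, and Statistical Power**: chi-square power for binomial primary outcomes, one proportion per branch.
- **Data Handling and Analysis**, bivariate analysis: "asking or telling HIV status to new sex partners [yes/no", given as an example of a primary outcome variable.
- **Multivariate analysis and analysis of treatment branches**: asking a new partner as the pretest term in logistic regression, and McNemar's test on disclosure with a new partner. The same part compares branches by linear regression on group means.

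No section says which form takes precedence.

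**The concern.** Partner serostatus in this trial is the participant's own knowledge, and asking is one way to gain it. Telling can prompt the partner to reciprocate. The variable that defines the strata can therefore be a consequence of the behaviour being scored. If a video makes men ask more, some partners who would have been of unknown status become known. The known-status stratum at follow-up then holds a different mix of partners from the one at baseline, and a different mix from that in a branch where asking did not rise. A difference in stratum means confuses the change in behaviour with the change in membership.

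Disclosure is one of three primary outcomes, and the videos are designed to raise it. Hypothesis 3a concerns new partners as a whole, so a set of stratum scores does not answer it directly. The power table does not describe those scores either.

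**Working it through.** **1. The plan's own figure.** The power table gives 0.936 for 0.30 against 0.45 with 400 per branch, at two-sided 0.05/10 = 0.005 (z = 2.807).

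- Null standard error: √(2 × 0.375 × 0.625 / 400) = 0.0342; times 2.807 = 0.0961.
- Alternative standard error: √((0.30 × 0.70 + 0.45 × 0.55) / 400) = 0.0338.
- With continuity correction: (0.15 − 1/400 − 0.0961) / 0.0338 = 1.52, power 0.936.
- Without it: (0.15 − 0.0961) / 0.0338 = 1.59, power 0.945.

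The corrected formula reproduces all 44 numeric cells of the table to within 1.3 points. The table is sound for an unsplit binary outcome.

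**2. Model for the split.** Let *a* be the probability that a new partner is asked, *r* the probability that his status is known if asked, and *u* the probability that it is known if not asked. Then:

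- asked, among known-status partners = *ar* / (*ar* + (1 − *a*)*u*)
- asked, among unknown-status partners = *a*(1 − *r*) / (*a*(1 − *r*) + (1 − *a*)(1 − *u*))

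The pairs of *a* come from the power table. The values of *r* and *u* are assumptions, since the protocol gives none. A known/unknown division is also an assumption, because the strata are not listed.

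**3. True rise 0.30 to 0.45, *r* = 0.9, *u* = 0.1.**

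- Known status: 0.27/0.34 = 0.794 becomes 0.405/0.46 = 0.880, a change of +0.086.
- Unknown status: 0.03/0.66 = 0.045 becomes 0.045/0.54 = 0.083, a change of +0.038.
- The true change is +0.15.

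**4. Range for the same true rise of 0.15.**

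| *r* | *u* | Change, known status | Change, unknown status |
| --- | --- | --- | --- |
| 1 | 0 | 0 | 0 |
| 0.9 | 0.05 | +0.051 | +0.036 |
| 0.9 | 0.1 | +0.086 | +0.038 |
| 0.9 | 0.2 | +0.128 | +0.042 |
| 0.8 | 0.4 | +0.159 | +0.089 |

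**5. Low baseline asking, 0.10 to 0.20, *r* = 0.9, *u* = 0.1.** Known status: 0.09/0.18 = 0.500 becomes 0.18/0.26 = 0.692. The change is +0.192 against a true +0.10, so this stratum overstates the rise.

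**6. Odds-ratio scale.** For 0.30 to 0.45 the overall odds ratio is (0.45/0.55) / (0.30/0.70) = 1.91. With *r* and *u* constant, it is also 1.91 in each stratum. The distortion is on the mean scale.

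**7. Power.** Take 400 men per branch with one new partner each (an assumption), 0.005 two-sided, and the uncorrected formula.

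- 0.30 to 0.45: unsplit 0.945; known-status stratum (400 × 0.34 = 136 against 400 × 0.46 = 184) 0.25; unknown-status stratum 0.14.
- 0.10 to 0.20: unsplit 0.88; known-status stratum 0.41, even though its difference is inflated.

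**The case against.** The strongest reply is that the protocol already contains a sound outcome. The power section and the bivariate and logistic analyses use a binary disclosure outcome with new partners and no serostatus split, and that form escapes the problem. This stands, and it limits the point to the form in the outcome table. It does not remove the point, because the table is where the primary variables are defined and nothing ranks the two forms.

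A second reply is that the survey is a separate file. The strata, the presence of an unknown category, the rule for assigning status, and whether the four variables are combined are all unseen. That is fair, and it is why the figures above are illustrations. The structural issue does not depend on those details. If there is an unknown category, unasked partners tend to collect there; if there is none, they may drop out of the score.

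A third reply is that a logistic model on a dichotomised item within strata would recover the odds ratio. It would, if *r* and *u* are constant, but the table calls for a continuous score and the between-branch analysis uses group means.

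A reader might go further and infer that status is usually known only because the man asked, so that an effective video would appear to do nothing. The protocol does not support this. No section says how status is learned. The row labels, such as "HIV Disclosure: Told partner(s); partners told", suggest that more than one route of disclosure is recorded. Zero change in every stratum needs *r* = 1 and *u* = 0 exactly, and at low baseline asking the known-status stratum overstates the rise.

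**Conclusion.** The point holds in a limited form. The disclosure outcome labelled primary is conditioned on a variable that asking or telling can change after randomisation, and it disagrees with the unsplit outcome in the hypotheses, the power table and the analysis section.

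The bias has no fixed direction. In the range shown, a true rise of 0.15 appears as anything from 0 to +0.159 among known-status partners and from 0 to +0.089 among unknown-status partners; a true rise of 0.10 from a low base appears as +0.192 among known-status partners. These sizes rest on assumed *r* and *u*, constant over time and across branches, on a known/unknown split, and on partner-level proportions standing in for person-level Likert means. For telling, the argument is the same in kind, but no size was calculated.

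**What to change.** In the outcome table, replace the two disclosure definitions with asking and telling across all new partners in the 60-day window, regardless of partner serostatus, in the yes/no form that the power and analysis sections already use. State whether asking and telling are two outcomes or one combined outcome, since the analysis text can be read either way. State also that the breakdown by partner serostatus is descriptive and not a basis for comparing branches. If a subgroup split is wanted, use the participant's own baseline HIV status, which the assigned branch cannot affect.

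The cost is one definition. If the survey has no overall item, one for asking and telling over all new partners may have to be added; the intention questions in Appendix F are already worded without a partner-serostatus split. The downside is that results by partner serostatus lose primary standing.
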